# A prospective, multicenter, randomized OCT study of early neointimal condition at first and second months after BuMA Supreme stent versus XIENCE stent implantation in high-bleeding-risk coronary artery disease patients: study protocol for a randomized controlled trial

**DOI:** 10.1186/s13063-019-3361-0

**Published:** 2019-06-07

**Keywords:** BuMA stent, Malposition, Optical coherence tomography, Stent-strut coverage, Bleeding risk, Coronary artery disease

## Abstract

**Background:**

Earlier vascular healing after drug-eluting stent (DES) implantation may reduce the incidence of late stent thrombosis and provide theoretical evidence to shorten dual antiplatelet therapy duration in patients with high bleeding risks. The BuMA supreme stent is a newly developed DES-coated with the sirolimus by using the international patent electronic grafted eG™ technology. Previous randomized trials showed that BuMA stents had better stent-strut coverage at 3-month follow-ups, which were evaluated by optical coherence tomography (OCT). However, there have been a limited number of studies that are directly evaluating the extent of neointima formation at the first and second months after stent implantation in high-bleeding-risk patients with coronary artery disease. This clinical trial is designed to demonstrate the non-inferiority of the BuMA supreme stent compared to the XIENCE stent in early neointimal formation.

**Methods/design:**

This is a prospective, multicenter, randomized trial. Forty patients will be assigned into the first-month OCT group, and another 40 patients into the second-month OCT group. The patients in each cohort will be randomized again into two groups in a 1:1 ratio, either being implanted with the BuMA Supreme stent or the Xience V/Prime/Xpedition stent. The primary endpoint is stent-strut neointimal coverage rate (%) at the first and second months, respectively. Secondary endpoints include neointimal hyperplasia area/volume, neointimal hyperplasia thickness, stent-strut malapposition rate, late lumen loss (LLL), restenosis rate, device/lesion/clinical success rate, device-oriented composite endpoints at the first and second months, stent thrombosis and other serious adverse events and bleeding events at follow-up.

**Discussion:**

The results will provide the first accurate imaging evidence on neointimal formation of the BuMA Supreme stent and the Xience stent at 1–2 months post PCI. The result should inspire further exploration and adjustment of DAPT treatments.

**Trial registration:**

ClinicalTrials.gov, ID: NCT02747329. Registered on 21 April 2016. Last updated 17 May 2018.

**Electronic supplementary material:**

The online version of this article (10.1186/s13063-019-3361-0) contains supplementary material, which is available to authorized users.

## Background

Drug-eluting stents (DES) reduce the rate of restenosis and consequent need for target lesion revascularization (TLR) compared with bare metal stents (BMS). However, impaired endothelialization increases the risk of late and very late stent thrombosis [1]. As a solution, the patient’s postoperative dual anti-platelet therapy (DAPT) treatment increases gradually from 1 month for the BMS to 6–12 months for DES post procedure, or even longer. But extension of DAPT increased the risk of bleeding, which raises another issue of how to shorten the DAPT period after the new DES implantation – which will benefit the patients with relatively high bleeding risk [2].

The BuMA stent (SINOMED, Beijing, China) is a novel, biodegradable, poly-lactic-co-glycolic acid polymer sirolimus-eluting stent (SES), with a thin-strut cobalt-chromium platform (80 μm), thin (200 nm) electro-grafting base between the polymer and stainless-steel stent strut. The BuMA Supreme SES has a pharmacokinetic polymer degradation/drug release profile where the top coat releases the drug relatively rapidly such that sirolimus release from the stents surface is nearly complete by 28 days after implantation [3]. The PIONEER trial showed that the BuMA stent did not meet the criteria for non-inferiority to zotarolimus-eluting stents (ZES) in terms of angiographic in-stent late lumen loss (LLL) at 9-month follow-up [4]. The study also showed that the BuMA SES was superior to the EXCEL SES in endothelialization at 3-month follow-up [5]. However, the earlier (≤ 2-month) endothelialization data are limited. This study can provide accurate imaging evidence on early neointimal formation of the BuMA and Xience stents, and provide evidence for further exploration and adjustment of DAPT treatment.

## Methods/design

### Study design

This is a prospective, multicenter, randomized clinical trial that should demonstrate the non-inferiority of the BuMA Supreme stent compared with the Xience stent on neointimal healing response evaluated by optical coherence tomography (OCT). In the current trial, the following devices will be used: BuMA Supreme stent – Biodegradable Polymer SES Coated Coronary Stent System manufactured by SINO Medical Sciences Technology Inc. and the Xience V/Prime/Xpedition stent – Durable Polymer everolimus-eluting Stent System manufactured by Abbott Company. A full range of commercially available guiding catheters, balloon catheters, and guidewires will be readily available.

### Patient enrollment

Eighty coronary artery disease (CAD) patients with a high bleeding risk will be included from eight centers, the major inclusion and exclusion criteria are summarized in Table 1. Patients will be randomized into two cohorts using a 1:1 ratio, 40 patients will be assigned into a first-month OCT group. The other 40 patients will be assigned into a second-month OCT group. The patients in each cohort will be randomized again into two groups in a 1:1 ratio, either receiving the BuMA Supreme stent or the Xience stent. The process of patient recruitment, enrollment and randomization is summarized in Figs. 1 and 2 shows the Standard Protocol items: Recommendations for Interventional Trials (SPIRIT) Figure for the trial.

**Table 1 Tab1:** Major inclusion and exclusion criteria

Inclusion criteria	
1. The age of patients is between18 and 85 years	
2. Symptoms and evidence of myocardial ischemia without raised troponin (e.g., stable or unstable angina, silent ischemia demonstrated by positive territorial functional study)	
3. CAD patients with a high risk of bleeding. Any one or more situation listed below can be considered the patient with high bleeding risk by the investigator [6]: a) Adjunctive oral anticoagulation treatment planned to continue after PCI b) Baseline Hb < 11 g/dl (or anemia requiring transfusion during the prior 4 weeks) c) Any prior intra-cerebral bleed at any time d) Any stroke during the past year e) Hospital admission for bleeding during the prior 12 months f) Non-skin cancer diagnosed or treated ≤ 3 years g) Planned daily NSAID or steroids for ≥ 30 days after PCI h) Planned major surgery (within 1 year) i) Renal failure (calculated creatinine clearance < 60 ml/min) j) Thrombocytopenia (< 100,000/mm^3^) k) Severe chronic liver disease (variceal hemorrhage, ascites, hepatic encephalopathy or jaundice) l) Patient with previous history of gastrointestinal bleeding m) Patient meets the following 2 or more factors: “aged female,” “diabetes,” “uncontrolled high blood pressure,” “heart failure”	
4. The patient has a planned intervention of up to two de novo lesions in different epicardial vessels	
5. Lesion(s) must have a visually estimated diameter stenosis of ≥ 70% and < 100%	
6. Reference vessel diameter (RVD) must be visually estimated ≥ 2.5 and ≤ 4.0 mm, and the lesion length must be no more than 40 mm	
7. The patient and the patient’s physician agree to the follow-up visits including angiographic follow-up and OCT controls at 1 or 2 month	
8. Written informed consent provided	
Exclusion criteria	
1. Left ventricular ejection fraction (LVEF) < 30%	
2. Patients expected not to comply with 1-month DAPT	
3. Chronic total occlusion (TIMI 0), left main lesion, intervention-required three-vessel lesions, branch vessel diameter ≥ 2.5 mm and bypass lesion	
4. Patients requiring a planned-staged PCI procedure more than 1 week after the index procedure	
5. Procedure planned to require non-study stents, or stand-alone POBA or stand-alone atherectomy	
6. Severe tortuous, calcified or angulated coronary anatomy of the study vessel that in the opinion of the investigator would result in suboptimal imaging or excessive risk of complication from placement of an OCT catheter	

*CAD* coronary artery disease, *DAPT* dual anti-platelet therapy, *OCT* optical coherence tomography *NSAID* non-steroidal anti-inflammatory drug, *PCI* percutaneous coronary intervention, *POBA* plain old balloon angioplasty

**Fig. 1 Fig1:**
[figure not shown]
Design of study. *OCT* optical coherence tomography, *CAD* coronary artery disease

**Fig. 2 Fig2:**
[figure not shown]
Standard Protocol Items: Recommendations for Interventional Trials (SPIRIT) Figure

### Randomization

This is a prospective, multicenter, randomized controlled clinical trial; the central randomized method based on the computer system was used in this trial. Patients with provided written, informed consent who meet the “all inclusion and no exclusion” criteria will be enrolled into the study. After the investigator fills in the randomized application form and logs into the randomization website, the computer system will automatically assign random number and corresponding treatment groups to patients according to the patient condition. After obtaining a randomized result, the investigator should record the random number and the corresponding stent information on the randomized application form and the original case history record. Patients will be treated by the system according to the requirement of the randomized groups (the treatment group/the control group). The investigator needs to print a random result list after randomization. The clinical center should archive the randomized list and other related documents (randomized application form) together in the folder. The folder should be archived well in preparation for inspection.

### Ethical and informed consent of clinical trials

This trial will be conducted in compliance with the current Helsinki Declaration, Medical Device Clinical Trail Regulations, International Conference on Harmonization (ICH) Good Clinical Practice (GCP) guidelines and relevant national regulations. Prior to initiation of the study, the investigator will submit copies of the protocol, informed consent form and all other relevant documents to the Institutional Review Board (IRB)/Ethics Committees (EC) for its review and approval. A copy of the written IRB/EC approval must be provided to the sponsor (or designee). Any amendments to the protocol, as well as possible associated information and consent form changes, will be submitted to the IRB/EC and written approval obtained prior to implementation. Documentation of serious adverse events in the clinical trials should be submitted to the IRB/EC in time. Eligible patients (and/or the patient’s parents or the patient’s legal guardian, if applicable) should be informed about the trial and have to sign an informed consent prior to the first study procedure. The contents of the trial, purpose of the trial, expected efficacy, possible adverse events and response to adverse events of the procedures and study should be explained to the patient. Informed consents are obtained from the investigators and participants or their legally authorized representatives, and both parties save a copy.

### Medication specification

DAPT is recommended for pre-procedure and post-procedure medication in accordance with the “Chinese guideline for percutaneous coronary intervention [7]”; the proposed dose is as follows. In consideration of patients with a high-risk of bleeding, the actual loading dose may vary based on the investigator’s discretion, which will not be deemed as protocol deviation.

For patients who are already on aspirin, a maintenance dose of 100–300 mg/qds will be administered. For patients not previously exposed to aspirin, a loading dose of aspirin 300 mg will be administered as the first dose 2 h before percutaneous coronary intervention (PCI), preferably within 24 h before PCI.

For patients already on clopidogrel, a maintenance dose of 75–150 mg clopidogrel will be administered within 6 h before PCI. For patients who not previously exposed to clopidogrel, a loading dose of 600 mg of clopidogrel will be administered within 6 h before PCI. For patients already on clopidogrel for more than 72 h, no more increased load is needed.

During the procedure, patients will receive appropriate heparin according to actual situation by investigator.

Post the procedure, a subcutaneous low-molecular-weight heparin injection is given if necessary, dual anti-platelet therapy with aspirin and clopidogrel is recommended, 75 mg clopidogrel and 100 mg aspirin once a day. DAPT is recommended for at least 3 months after PCI, a maintenance of DAPT, a reduction in antiplatelet therapy or less antiplatelet treatment time using DAPT is permitted in patients by the investigator according to patient’s specific bleeding and ischemic status.

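### The aspirin maintenance dose is printed with a four-times-daily frequency, most likely a slip for once daily

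*Protocol article*

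**What the plan says.** The Medication specification section recommends dual antiplatelet therapy before and after the procedure in line with a cited national guideline, and introduces its regimen with the words "the proposed dose is as follows". The doses relevant here are:

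- **Patients already on aspirin:** "a maintenance dose of 100–300 mg/qds will be administered".
- **Patients new to aspirin:** "a loading dose of aspirin 300 mg will be administered as the first dose", timed before the procedure.
- **Patients already on clopidogrel:** "a maintenance dose of 75–150 mg clopidogrel will be administered within 6 h before PCI".
- **After the procedure:** "75 mg clopidogrel and 100 mg aspirin once a day".

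Two clauses give the investigator latitude. The first, in the opening paragraph, says that "the actual loading dose may vary based on the investigator’s discretion" and that this is not a protocol deviation. The second, in the paragraph on treatment after the procedure, says that "a reduction in antiplatelet therapy or less antiplatelet treatment time using DAPT is permitted in patients by the investigator", depending on the patient's bleeding and ischemic status.

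The Abbreviations section has no entry for *qds*, and the frequency is not restated or corrected anywhere else in the article.

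**The concern.** The frequency attached to the aspirin maintenance dose does not fit its surroundings. Four doses a day would give a daily total several times that of the only other repeated aspirin dose in the section, which is given once a day. The parallel clopidogrel maintenance sentence has no multiple-daily frequency either.

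What is at stake is dosing safety. Table 1 restricts entry to patients at high bleeding risk, and among the qualifying conditions are "Patient with previous history of gastrointestinal bleeding" and oral anticoagulation planned to continue after the procedure. These are the patients for whom an aspirin frequency most needs to be right, even when the dose is only a recommendation. Bleeding events are also among the secondary clinical endpoints.

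No statistical consequence is alleged. The sentence applies equally to both stents, so the coverage comparison, its non-inferiority margins and the power statement are not affected.

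**Working it through.** The article gives no daily total for this dose, so there is no figure of its own to reproduce. The check is unit arithmetic.

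**Inputs, all from Medication specification**

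- Maintenance dose, single administration: 100 to 300 mg.
- Aspirin after the procedure: 100 mg, once a day.
- Loading dose for patients new to aspirin: 300 mg, given once.

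One input comes from general usage and not from the article: *qds* means 4 administrations a day. Once daily means 1.

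**Formulas**

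Daily total = single dose × administrations per day.

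Ratio = daily total ÷ daily dose after the procedure (100 mg).

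| Reading | Lower daily total | Upper daily total | Ratio to 100 mg/day |
|---|---|---|---|
| Four times daily (as printed) | 4 × 100 = 400 mg | 4 × 300 = 1200 mg | 400/100 = 4 to 1200/100 = 12 |
| Once daily | 1 × 100 = 100 mg | 1 × 300 = 300 mg | 100/100 = 1 to 300/100 = 3 |

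**Comparison with the loading dose.** This needs care, because the load is a single dose and not a daily total. Each single maintenance dose is 100/300 = 0.33 to 300/300 = 1.0 times the load, so no single administration exceeds it. On the printed frequency the daily total would be 400/300 = 1.33 to 1200/300 = 4.0 times the load. That ratio sets a daily total against a single dose, so it is only supporting evidence; the day-for-day comparison with the dose after the procedure is the sound one.

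**Does either latitude clause cure the sentence?** The clause on discretion names the loading dose only. The clause on reduction belongs to the paragraph on treatment after the procedure. Neither clearly reaches the maintenance dose for patients already on aspirin.

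**Which reading fits?** The once-daily reading gives 100 to 300 mg a day. It agrees with the frequency stated for aspirin after the procedure, its daily total never exceeds the load, and it matches the clopidogrel sentence. The four-times-daily reading has none of these properties.

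The sentence does not itself say that the dose is given before the procedure. That follows from its position beside the pre-procedure loading doses and ahead of the paragraphs on treatment during and after the procedure.

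**The case against.** The strongest reply is that this is an editorial slip with no bearing on the trial's inference. Several parts of it carry weight.

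- **The unit is malformed.** A slash normally introduces a unit such as a day, so milligrams per four-times-daily is not a proper expression, and 400 to 1200 mg a day is one interpretation of a garbled string. This stands in part. The multiple of 4 to 12 describes a reading that was probably not intended, and a clinician may well infer once daily.
- **Exposure is limited.** The sentence covers only patients already on aspirin, and by its position it concerns the period before the procedure. Afterwards the section sets 100 mg once a day and allows reduction. This stands. No duration is given, so no expected harm can be calculated.
- **The regimen is advisory.** It is presented as a proposal under a guideline. This stands, but a recommended dose should still carry the right frequency, and the sentence itself is worded as what will be given.
- **The intended frequency cannot be confirmed.** Neither the full protocol nor the guideline is shown, and the slip may have arisen in translation or journal editing. This stands. Confidence is high that the printed frequency conflicts with the rest of the section, but lower that once daily was meant, and nothing is known about the wording that sites received.

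Condensation for a journal does not explain the problem. The article has not left the frequency to a fuller document; it prints one that does not fit. Nothing in the reply shows that the sentence is right as it stands.

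**Conclusion.** The concern holds as a minor wording error. As printed, the recommended aspirin maintenance dose amounts to 400 to 1200 mg a day, which is 4 to 12 times the once-daily dose recommended after the procedure. Read as once daily, it is 1 to 3 times that dose and consistent with the section.

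The conclusion rests on the usual meaning of *qds*, which the article does not alter. That once daily was intended is the most plausible reading, but it remains an inference. No claim is made that any patient received the higher dose, or that the endpoint, the power or the comparison between stents is affected.

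**What to change.** Check the dose in the full protocol and in the guideline that the section cites. If they confirm it, replace the printed frequency so that the maintenance dose for patients already on aspirin reads 100–300 mg once daily. If they show a different intended frequency, print that one in full words instead of an abbreviation.

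If the protocol used at the sites carries the same wording, send the sites a short clarification; otherwise correcting the article is enough.

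The change is a single term. It has no statistical cost and requires no change to the design, sample size or analysis.

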### OCT and QCA evaluation

The OCT and quantitative coronary angiography (QCA) results of this study will be evaluated by an independent core laboratory (PLA general Hospital, Beijing, China) in a blind manner. According to the standard procedure, imaging discs of the baseline procedure, baseline OCT, follow-up angiography and OCT (1 month or 2 months), and any unintended angiography will be sent to the coronary angiography core laboratory to complete the qualitative and quantitative analysis by the experienced image analyst blinded to the treatment protocol. Standard QCA methodology was used including analysis of stent and peri-stent segments defined as spanning 5 mm proximal and distal to the stent edge. Binary restenosis was defined in every segment (proximal, distal and in-stent) as > 50% diameter stenosis at follow-up. LLL was defined as the difference between follow-up and post-procedure minimal lumen diameter.

OCT parameters were calculated and defined as follows [8, 9]: neointimal thickness was measured as the perpendicular distance between the endoluminal surfaces of the neointima to the stent strut. Stent and lumen areas will be measured, and the neointimal hyperplasia area is calculated as the stent area minus the lumen area. The neointimal hyperplasia volume is calculated as the sum of the neointimal hyperplasia areas. The absence of definite neointima over the stent strut was defined as an uncovered stent strut. The distance between the inner surface of the strut reflection and the vessel wall was measured by extending the contours of the walls on the outside of the strut shadow. Stent-strut malapposition was defined as struts with detachment from the vessel wall > 138 μm for the BuMA and > 155 μm for the XIENCE (stent-strut thickness + coating thickness + OCT resolution limit of 20 μm).

### Study endpoints and clinical follow-up

The primary endpoint is the stent-strut neointimal coverage rate (%) by OCT assessment at 1 month and 2 months, respectively. Secondary OCT endpoints include neointima hyperplasia area/volume, neointimal hyperplasia thickness and the stent-strut malapposition at 1 or 2 months’ follow-up, respectively. Secondary angiographic endpoints include LLL, restenosis rate of in-stent/in-segment at 1 or 2 months’ follow-up, respectively. Secondary clinical endpoints include device/lesion/clinical success rate, device-oriented composite endpoints and its individual components, other serious adverse (MI, TLR and stent thrombosis) and bleeding events at 1 or 2, 3, 6 months, 1 year and 2 years.

Target lesion failure was defined as the composite of cardiac death, target vessel myocardial infarction (MI), and ischemia-driven TLR. MI was adjudicated according to the third universal definition of MI [10]. Stent thrombosis (definite and probable) was defined according to the Academic Research Consortium (ARC) classification. All clinical events were adjudicated by an independent Clinical Events Committee (CEC). Device success was defined as attainment of < 30% residual stenosis of the target lesion by visual assessment. Lesion success was defined as attainment of < 30% residual stenosis, TIMI 3 flow, and no residual dissection or thrombosis of the target lesion using any percutaneous method. Clinical success was defined as attainment of lesion success of the target lesion and no in-hospital major adverse cardiac event.

Angiography and OCT investigations are conducted at 1 or 2 months post PCI. Clinical follow-up visits or telephone follow-up will be conducted at the first, second, third, sixth month, or 1 to 2 years post PCI.

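### Device success as printed is not tied to the assigned stent, so a failed study stent rescued with another device counts as a device success

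*Protocol article*

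**What the plan says.** The protocol article lists three procedural success rates among the secondary endpoints: "Secondary clinical endpoints include device/lesion/clinical success rate". Study endpoints and clinical follow-up then defines each in one sentence.

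- Device success: "Device success was defined as attainment of < 30% residual stenosis of the target lesion by visual assessment". There is one condition, and no device is named.
- Lesion success: "Lesion success was defined as attainment of < 30% residual stenosis, TIMI 3 flow, and no residual dissection or thrombosis of the target lesion", with the closing words "of the target lesion using any percutaneous method". The stenosis threshold is the same, two criteria are added, and the means of treatment is left open.
- Clinical success: "Clinical success was defined as attainment of lesion success of the target lesion and no in-hospital major adverse cardiac event".

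On whether another device can enter the procedure, Table 1 under Patient enrollment excludes a "Procedure planned to require non-study stents, or stand-alone POBA or stand-alone atherectomy". That criterion covers what is planned beforehand. It does not cover what happens when a study stent cannot be delivered or deployed.

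**The concern.** A device success rate is reported to show how often the randomized stent did its job in the procedure. The event it most needs to register is a study stent that fails and is replaced by something else. Under the printed sentence that event is a success as long as the lesion ends below 30% stenosis, whatever produced the result. The rate then describes the final angiographic result of the procedure, which lesion success already describes in more detail, and says nothing specific about the BuMA Supreme or the Xience stent. If one stent needed more rescues than the other, this endpoint would not show it.

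**Working it through.** The plan states no figure for device success, so there is nothing to reproduce. The check is one of logic, followed by an illustration of size.

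**Step 1: code the definitions.** For each treated lesion let

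- R = residual stenosis below 30%
- T = TIMI 3 flow
- C = no residual dissection or thrombosis
- S = result achieved with the assigned study stent

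As printed in Study endpoints and clinical follow-up:

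- device success = R
- lesion success = R and T and C
- clinical success = lesion success and no in-hospital major adverse cardiac event

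S appears in none of them.

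**Step 2: enumerate.** With one stenosis reading for both endpoints there are 2 × 2 × 2 × 2 = 16 combinations.

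| Question | As printed | With S added to device success |
|---|---|---|
| Combinations with lesion success but not device success | 0 | 1 (R, T, C met; S not met) |
| Combinations counted as device success although S is not met | 4 (R met, S not met, T and C free) | 0 |

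As printed, therefore, device success ≥ lesion success ≥ clinical success in every dataset. Once S is required, the rescued case becomes a lesion success with a device failure, and the device rate can fall below the lesion rate.

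**Step 3: test the assumption.** The lesion success sentence does not say how stenosis is read. If it used a different reading from device success, there would be 32 combinations, and 2 of them would give lesion success without device success. The ordering in step 2 thus depends on a common reading. The failure to register a rescue does not: device success still ignores S.

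**Step 4: illustrate the size.** Sample size of clinical trials gives 20 subjects per group; with two cohorts that is 20 + 20 = 40 patients per device. Statistical analysis takes the individual as the unit. Assume that every final result is below 30% and that b patients had a failed study stent rescued with another device. The range of b is an assumption, because the documents give no bail-out rate.

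- As printed: 40/40 = 100% for any b.
- With S required: (40 − b)/40.

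| b | As printed | With the assigned-stent condition |
|---|---|---|
| 0 | 100% | 100% |
| 1 | 100% | 39/40 = 97.5% |
| 2 | 100% | 38/40 = 95% |
| 4 | 100% | 36/40 = 90% |

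**Step 5: would a test result change?** Statistical analysis names chi-square or Fisher's exact test for categorical variables. With 40 per device and no failures on the other side, the two-sided Fisher p-value is 2 × C(40,b)/C(80,b).

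- b = 2: 2 × 780/3,160 = 0.49
- b = 4: 2 × 91,390/1,581,580 = 0.12
- b = 6: 2 × 3,838,380/300,500,200 = 0.026

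Over the illustrated range only the reported rate changes, not the test conclusion.

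**The case against.** The best defence is that these are condensed one-line definitions. The label itself says device, and the open-ended choice of method is attached to lesion success only, so a contrast with the study stent was probably intended and the full protocol may spell it out. That is a fair guess at intent. It does not rescue the printed rule: the article does not leave device success undefined but prints a complete definition, and anyone applying it would score a rescued failure as a success. Nothing elsewhere in the article supplies the missing condition.

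It is also fair to say that nesting alone is no fault, since clinical success is deliberately nested in lesion success, and that the likely numbers are too small to alter a test. Both points stand, and they limit the weight of the finding.

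A reader might infer several stronger things that the document does not support.

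- **That the definition favours the non-inferiority claim by pulling the arms together.** Non-inferiority is set only for neointimal coverage, with margins of 3.6% and 2.4%. No margin is attached to device success.
- **That an unblinded operator reads the stenosis.** The text says only that the assessment is visual and names no reader.
- **That QCA must replace the visual reading.** The OCT and QCA results "will be evaluated by an independent core laboratory", but using that measurement here would be a preference; no passage contradicts the visual choice.
- **That the missing TIMI criterion is a defect.** Device and lesion success may reasonably differ on flow.
- **That bail-outs would go unreported altogether.** The definition of one rate does not show that, and a rescue leaving 30% stenosis or more would still count as a failure.

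**Conclusion.** The point holds, as a minor one. The printed definition of device success lacks the condition that makes it about the device, and the exclusion criteria leave room for the event that it then misclassifies. That conclusion follows from the wording alone. The further statement that device success can never be lower than lesion success holds only if both use the same stenosis reading, which is the plain reading but is not stated.

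The possible overstatement is 2.5 percentage points for each rescued patient out of 40 (1/40), provided all final results are below 30%. How many such patients there would be is unknown from the documents. The effect is confined to one secondary procedural rate; the primary endpoint, its margins and the sample size are untouched.

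**What to change.** Add one clause, so that device success means residual stenosis below 30% of the target lesion, by visual assessment, achieved with the assigned study stent only. State beside it that a lesion finished with another device is a device failure and may still be a lesion success. It would help to say in the same place that lesion success uses the same stenosis reading.

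The cost is small: no added visit or imaging. The article says that the investigator records the stent corresponding to the randomized result; it does not say that the device actually implanted is captured, so the case report form should be checked for that item. The reported device success rate may come out slightly lower than under the present wording.
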